## Abstract

**Background:**

In chronic obstructive pulmonary disease, the prognosis for patients who have survived an episode of acute hypercapnic respiratory failure due to an exacerbation is poor. Despite being shown to improve survival and quality-of-life in stable patients with chronic hypercapnic respiratory failure, long-term noninvasive ventilation is controversial in unstable patients with frequent exacerbations, complicated by acute hypercapnic respiratory failure. In an uncontrolled group of patients with previous episodes of acute hypercapnic respiratory failure, treated with noninvasive ventilation, we have been able to reduce mortality and the number of repeat respiratory failure and readmissions by continuing the acute noninvasive ventilatory therapy as a long-term therapy.

**Methods:**

Multi-center open label randomized controlled trial of 150 patients having survived an admission with noninvasive ventilatory treatment of acute hypercapnic respiratory failure due chronic obstructive pulmonary disease. The included patients are randomized to usual care or to continuing the acute noninvasive ventilation as a long-term therapy, both with a one-year follow-up period. The primary endpoint is time to death or repeat acute hypercapnic respiratory failure; secondary endpoints are one-year mortality, number of readmissions and repeat acute hypercapnic respiratory failure, exacerbations, dyspnea, quality of life, sleep quality, lung function, and arterial gases.

**Discussion:**

Though previous studies of long-term noninvasive ventilation have shown conflicting results, we believe the treatment can reduce mortality and readmissions when applied in patients with previous need of acute ventilatory support, regardless of persistent hypercapnia.

**Trial registration:**

clinicaltrials.org: NCT01513655 16-Jan-2012.

## Background

Noninvasive ventilation (NIV) has been shown to improve survival in patients with chronic obstructive pulmonary disease (COPD), admitted with acute hypercapnic respiratory failure (AHRF) [1]; and NIV is recommended as a treatment of AHRF due to COPD [2]. COPD patients having survived AHRF have a poor prognosis; Chu et al. have shown one-year risks of readmission of 79.9 %; of a new life-threatening event (death or repeat AHRF) of 63.3 %; and of death of 49.1 % [3].

Hypothetically, long-term NIV (LTNIV) can improve the prognosis for severe COPD. The majority of trials have focused on patients with chronic hypercapnic respiratory failure due to stable COPD (i.e., patients with no exacerbations prior to LTNIV initiation); and their results have been conflicting [4]. However, in 2014, Köhnlein et al. published the results of a large randomized controlled trial (RCT) of LTNIV for stable patients with an arterial CO_2_ tension (*P*_a,CO2_) of 7 kPa or higher [5]: The patients treated with LTNIV had a one-year mortality of 12 % vs. 33 % for the controls; and the patients treated with LTNIV scored higher in health-related quality-of-life (HRQoL).

Three RCTs have studied the effects of LTNIV for unstable COPD, i.e., where the participants were enrolled after an admission with NIV treatment of AHRF: Cheung et al. and found that the patients treated with LTNIV had a lower rate of repeat AHRF (38.5 %/year vs. 60.2 %/year, *p* = 0.039) [6]; and Funk et al. found that the LTNIV group had a longer mean time to clinical worsening (391 days vs. 162 days; *p* = 0.0018) [7]. However, the largest RCT by Struik et al., showed no differences between the LTNIV group and the controls [8].

Little is known of what predicts AHRF in severe COPD. However, based on the large ECLIPSE study on exacerbations of COPD, Hurst et al. [9] and Müllerova et al. [10] showed that previous exacerbations predict new exacerbations [9]; and that previous admissions due to exacerbations of COPD predict new admissions and death [10].

We assume that previous admissions with AHRF due to COPD could predict new admissions with AHRF and need of NIV, as well as death.

We retrospectively analyzed 20 patients who were treated with LTNIV and followed at our pulmonary ward. The patients were offered LTNIV if they had been admitted for NIV treatment of AHRF at least twice. We found that the patients’ number of AHRF episodes and admissions due to COPD decreased significantly. And only four of the patients (20 %)—considerably less than the 49.1 % showed by Chu et al.—died within one year after initiation. Furthermore, these highly selected patients tolerated LTNIV well.

### Aim

The aim of this RCT is to investigate whether LTNIV can reduce mortality or repeat AHRF in patients who have been admitted for NIV treatment of AHRF due to COPD; and, secondarily, whether LTNIV can reduce mortality per se and the number of repeat AHRF, readmissions, and exacerbations, and improve quality of life.

## Methods/Design

COPD patients who are admitted for NIV treatment of AHRF (pH < 7.35 and *P*_a,CO2_ > 6 kPa) at Gentofte, Bispebjerg, Hvidovre or Herlev Hospitals in Greater Copenhagen are eligible. The patients must be optimally treated according to GOLD guidelines [2]. The patients must reside in the Capital Region, be able to give a verbal consent and sign a written consent form, and understand Danish.

The patients are excluded if they cannot comply with NIV or have a respiratory rate <12/min, severe hypoxia requiring more than 15 L O_2_/min, or a high risk of aspiration, recent abdominal, facial or upper airway surgery, malignancy or life expectancy of less than 6 months because of diseases other than COPD, known obstructive sleep apnea syndrome (OSAS), or a *St*HCO_3_^−^ less than 20 mmol/L.

### Design

The study is a multi-center randomized, controlled, open-label study. The participants are included during an admission with NIV treatment of AHRF due to COPD. If the patient gives consent (see below), he or she is randomized to either LTNIV or usual care. The acute NIV therapy is continued for as long the patient presents a hypercapnic acidosis or severe dyspnea without NIV; hereafter, NIV is ceased in the patients in the control group, whereas it is continued with the same settings in the LTNIV patients. When stable and when deemed appropriate by a physician, the patients are discharged.

The included patients will be given the possibility of contacting an acute hotline, operated by a nurse.

One week after discharge, all patients are visited by a nurse. The patients are followed in the outpatient departments with visits 1, 3, 6, 9, and 12 months after discharge.

A participant who is readmitted will not be re-randomized. If the participant is in the intervention group, LTNIV is resumed, if paused.

### Consent

When stabilized and able to have a small pause from NIV, the patient is presented to the study. If interested, the patient is formally informed of the study by one of the attending physicians. This is typically 2 days after admission, although individual. The information session is held with a physician who has devoted time for this and who is not disturbed. When informed, the consent form is signed by the patient and the informing physician. If the participant wants time for consideration, a new session will be planned one or two days later.

No individual data will be published.

### Intervention

For the intervention group, the acute NIV treatment is continued as LTNIV with the pressures and settings which had reversed the respiratory failure and the hypercapnic acidosis. The participant is offered to initiate an average volume-assured pressure support, but this is not mandatory.

Before discharge, the participant and caregivers are trained in handling and cleaning the ventilator, tubes, masks, etc. The participant is told to use the ventilator for a minimum of six hours of daily, preferably during sleep.

At the home visits and outpatient consultations, LTNIV is optimized according to the participant’s requests or complaints.

One month after discharge, LTNIV participants who have had only this one episode of AHRF and who do not feel a subjective improvement are offered to pause the LTNIV therapy, provided they have not had any of the following after discharge: exacerbation; need for antibiotics, increased oral corticosteroids, or inhaled medicine; hospitalization or visit to an emergency room or emergency physician due to COPD; fever of 38 °C or higher for at least one day; increased or purulent expectoration; or increasing dyspnea for at least one day.

If it is agreed to pause LTNIV, the participant is instructed to resume LTNIV at one or more of the above symptoms.

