### Sample size/power calculation

Chu et al. showed that the one-year risk of death *or* repeat AHRF for COPD patients having survived an admission with NIV treatment of AHRF is 63.3 % [3]; and, for the LTNIV group in the RCT by Cheung et al., this risk was 38.5 % [6].

We use these risks for the power calculation. We accept a 0.05 risk of type 1 error (α) and 0.2 of type 2 error (β). With a power of 0.8, the needed sample size is 120. With an expected dropout of 20 %, we intend to include 150 participants, 75 in each arm.

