### Data processing

The primary outcome is the difference in time to death *or* AHRF between the LTNIV group and the control group, analyzed as an Intention-To-Treat analysis and calculated in a Cox proportional hazards regression, using Kaplan-Meier and log rank.

The differences between the study’s two groups will be computed using *X*^2^-statistics for the dichotomous variables and t-tests for the continuous variables, assuming that data will follow a normal distribution. Differences in time to a given event are calculated in a Cox proportional hazards regression, using Kaplan-Meier survival statistics and log rank.

For all comparisons, *p* < 0.05 is the level of significance.

For the sample size calculation, we used SAS (Statistical Analysis System, version 9.4).

We will use the latest versions of SAS for the statistical analyses.

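### First versus repeat AHRF is treated as prognostic and decides who may pause LTNIV, but the stated primary comparison makes no use of it

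*Protocol article*

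**What the plan says.** - **Prognostic assumption (Background).** "We assume that previous admissions with AHRF due to COPD could predict new admissions with AHRF and need of NIV, as well as death". These are the two components of the primary outcome, death or repeat AHRF.
- **Own experience (Background).** In the uncontrolled series of 20 patients, "The patients were offered LTNIV if they had been admitted for NIV treatment of AHRF at least twice".
- **Eligibility (Methods/Design).** A current admission with NIV for AHRF is enough. No earlier episode is required, so patients in their first episode can enter.
- **Treatment rule (Intervention).** The rule for month 1 reads: "LTNIV participants who have had only this one episode of AHRF and who do not feel a subjective improvement are offered to pause". None of a list of events or symptoms may have occurred since discharge, and LTNIV is resumed if one of them appears. Under Design, it is also resumed on readmission.
- **Randomisation.** 1:1, in blocks within each centre. Episode history is not a factor.
- **Primary analysis (Data processing).** Time to death or AHRF is "analyzed as an Intention-To-Treat analysis and calculated in a Cox proportional hazards regression, using Kaplan-Meier and log rank". No covariate or stratum is named.

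**The concern.** One baseline characteristic, whether the index admission is the first AHRF episode, does two jobs in this protocol. It is assumed to be prognostic, and it decides who in the LTNIV arm may later be offered a pause. In the described primary comparison it does nothing.

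This has two consequences. First, the LTNIV arm may contain two patterns of use: ongoing treatment in patients with repeat AHRF, and for some first-episode patients treatment on demand after month 1. If the result is weak or null, the comparison as described gives no view of whether LTNIV has little effect, whether the effect is confined to one group, or whether time off treatment diluted it. Removing pausers afterwards would not help. They are selected on their course after randomisation and have no identifiable counterparts among controls.

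Second, if the factor is as prognostic as assumed, leaving it out of the Cox model pulls the hazard ratio towards 1 and costs some power.

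**Working it through.** **Inputs.** From the sample size section: the control "one-year risk of death *or* repeat AHRF for COPD patients having survived an admission with NIV treatment of AHRF is 63.3" %, and for LTNIV "this risk was 38.5" %, both taken as stated there. Also α 0.05 (two-sided assumed), power 0.8 and 20 % dropout. The documents do not give the share of first-episode patients, the share who pause, or the strength of the prognostic factor. These are assumptions, shown over a range.

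**1. The plan's own figure.** The article states: "With a power of 0.8, the needed sample size is 120". Two proportions, unpooled variance:

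n per arm = (1.960 + 0.842)² × [0.633 × 0.367 + 0.385 × 0.615] / (0.633 − 0.385)² = 59.9, rounded up to 60.

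That gives 120 in total, and 120/0.8 = 150. Both figures reproduce, so the arithmetic is not at fault. The 20 % inflation is for dropout; no allowance for planned pausing is stated. With the pooled z-test, power at 60 per arm is 0.78 (log-rank equivalent 0.81).

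**2. Implied hazards.** Cumulative one-year hazards are −ln(0.367) = 1.002 for control and −ln(0.615) = 0.486 for LTNIV. The hazard ratio is 0.486/1.002 = 0.485.

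**3. Pausing.** Suppose a share q of the LTNIV arm pauses at month 1.

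- Worst case, control hazard for the remaining 11 months: pauser risk = 1 − exp[−(0.486/12 + 1.002 × 11/12)] = 61.7 %.
- Half the log-hazard effect kept: hazard 1.002 × √0.485 = 0.698, so pauser risk = 1 − exp[−(0.486/12 + 0.698 × 11/12)] = 49.4 %.

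Arm risk = q × pauser risk + (1 − q) × 38.5 %. Power is for the pooled z-test against 63.3 %, 60 per arm.

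| q | Arm risk, worst case | Power | Arm risk, half effect kept | Power |
|---|---|---|---|---|
| 0 | 38.5 % | 0.78 | 38.5 % | 0.78 |
| 10 % | 40.8 % | 0.70 | 39.6 % | 0.74 |
| 20 % | 43.1 % | 0.60 | 40.7 % | 0.70 |
| 30 % | 45.5 % | 0.50 | 41.8 % | 0.66 |

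**4. What adjustment gains.** In simulated trials of 60 per arm with half the patients first-episode, adding the factor to the Cox model gained about 1 to 2 points of power at an assumed prognostic hazard ratio of 1.5 to 2, and about 8 points at 3. A repeat with 4,000 trials per setting agreed at 1.5 and 3 and gave about 3 points at 2. The gain comes from the prognostic factor and does not restore power lost to pausing.

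**5. What a first/repeat comparison can show.** Expected events are 120 × (0.633 + 0.385)/2 = 61. For a hazard ratio of 0.485 in one group and 1.0 in the other, the standard error of the difference in log hazard ratios is √(4/d₁ + 4/d₂), and |ln 0.485| = 0.724.

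- Events split 50:50 (30.5 and 30.5): SE 0.512, z = 1.41, power about 29 %.
- Events split 30:70 (18.3 and 42.8): SE 0.558, z = 1.30, power about 25 %.

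**The case against.** The strongest reply has five parts.

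- **The rationale is wider than the 20-patient series.** A reader might infer that first-episode patients fall outside the trial's rationale. The documents do not support this. The cited randomised trials enrolled after an AHRF admission, both sample-size risks come from patients after such an admission, and the Aim covers everyone admitted for NIV treatment of AHRF. Only the trialists' own series required two admissions. This stands.
- **The prognostic sentence is tentative.** It gives no effect size, and previous admissions could include the index one. So the gain from adjustment can only be shown over a range. But the pause rule separates first from repeat episodes explicitly, so the distinction is the protocol's own.
- **The analysis plan is not shown.** A reader might infer that the trial ignores episode history altogether. That cannot be said: covariates and subgroups may be set out in the full protocol or SAP. The point here is limited to the primary comparison that the article does describe, which can be improved at little cost.
- **A null result would not be uninterpretable.** A reader might infer that it would be. Intention-to-treat validly estimates the effect of the policy described under Intervention, and daily use is read from the ventilator at discharge and at outpatient visits. This stands; the loss is in explaining the result.
- **The pause is narrow.** It needs no subjective improvement, no listed event since discharge, and agreement, and it is reversed at symptoms or readmission. Nothing supports inferring that first-episode patients would be largely off treatment. Event-free first-episode patients may also have a below-average hazard, so the worst-case column probably overstates the loss.

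**Conclusion.** The point holds as a modest, correctable weakness in the stated analysis. The protocol assumes that previous AHRF is prognostic and uses it to decide who may pause LTNIV, yet the primary Cox and log-rank comparison makes no use of it. Validity under intention-to-treat is not affected.

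The direct statistical cost of omitting the factor is small unless it is strongly prognostic: a few points of power at a hazard ratio of 1.5 to 2, about 8 points at 3. The larger figures, power of 0.70, 0.60 and 0.50, describe worst-case dilution from pausing at assumed shares of 10, 20 and 30 %. They show what might need explaining, not what adjustment would recover.

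Estimates by first and repeat episode would be imprecise and could not settle the matter alone. They are nevertheless the one view of the group offered the pause that preserves randomisation, because episode history is fixed at baseline in both arms. Whether the pause rule is clinically right is not judged here.

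**What to change.** Keep the intention-to-treat comparison and the pause rule as they are, and make four changes.

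1. Record at baseline, in both arms, whether the index admission is the first AHRF episode or a repeat. The LTNIV arm already needs this to apply the pause rule.
2. Add this factor to the primary Cox model, with centre included as the randomisation stratum.
3. Pre-specify the LTNIV effect in first-episode and in repeat-AHRF patients as a supportive, exploratory analysis. State that an interaction test has only about 25 to 29 % power even for a hazard ratio of 0.485 versus 1.0.
4. Report how many participants paused and their time off LTNIV, from the ventilator data already read at visits.

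The cost is one extra baseline item for controls and a few lines in the analysis section, with no extra patients or procedures. The drawback is that the subgroup estimates will be imprecise and must be labelled so.

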### Randomization

A total of 150 COPD patients will be included from the four wards. The participants are randomized to LTNIV or usual care in a 1:1 ratio, using a computer-generated block-randomization for each center. The participant is presented with a sealed envelope containing a piece of paper with either “A” (= LTNIV) or “B” (= usual care). The randomization list is stored at Gentofte Hospital in a sealed envelope. 50 sealed envelopes are prepared for each center.

### Outcomes

Primary outcome is difference in time to death *or* repeat AHRF between the study’s two groups. AHRF is defined as a pH < 7.35 and a *P*_a,CO2_ > 6 kPa despite optimal treatment according to GOLD guidelines, i.e., nebulized bronchodilators and intravenous corticosteroids [2].

The secondary outcomes are differences in the following variables; one-year mortality, admissions due to COPD; admissions due to repeat AHRF; visits to the emergency department or to an emergency physician due to COPD; exacerbations treated with oral corticosteroids or oral antibiotics; body mass index; forced expiratory volume in one second (FEV_1_); cost efficiency; health-related quality-of-life (HRQoL), measured by COPD Assessment Test (CAT) and Severe Respiratory Insufficience Questionnaire (SRI); sleep quality, measured by the Epworth Sleepiness Scale (ESS); apnea/hypopnea index (AHI); and Medical Research Council's Dyspnea scale (MRCD).

### Sample size/power calculation

Chu et al. showed that the one-year risk of death *or* repeat AHRF for COPD patients having survived an admission with NIV treatment of AHRF is 63.3 % [3]; and, for the LTNIV group in the RCT by Cheung et al., this risk was 38.5 % [6].

We use these risks for the power calculation. We accept a 0.05 risk of type 1 error (α) and 0.2 of type 2 error (β). With a power of 0.8, the needed sample size is 120. With an expected dropout of 20 %, we intend to include 150 participants, 75 in each arm.

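### The 38.5% LTNIV risk behind the sample size is described in two incompatible ways, so the stated 80% power for death or repeat AHRF is not supported as written

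*Protocol article*

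**What the plan says.** In the protocol article, Outcomes, the primary outcome is the difference in time to death or "repeat AHRF between the study’s two groups". It is a composite.

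Sample size/power calculation gives the control figure, from reference 3, as the one-year risk of death or "repeat AHRF for COPD patients having survived an admission with NIV treatment of AHRF is 63.3" per cent. For the LTNIV group of an earlier RCT (reference 6) it then says "this risk was 38.5" per cent, so the same composite is meant. It continues "We use these risks for the power calculation" and concludes "With a power of 0.8, the needed sample size is 120", raised to 150 for 20% dropout.

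The Background agrees on the control figure, a one-year risk "of a new life-threatening event (death or repeat AHRF) of 63.3" per cent. For the RCT in reference 6 it reports something else: a "lower rate of repeat AHRF (38.5 %/year vs. 60.2 %/year". Death is not part of that description. The Discussion likewise credits the two smaller RCTs with fewer repeat AHRF episodes and less clinical worsening, and mentions no composite with death.

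**The concern.** One number from one source carries two labels. In the sample-size section it is the risk of death or repeat AHRF; in the Background it is a rate of repeat AHRF alone. Both cannot be right. The authors label the 63.3% explicitly as a composite in the same Background section, so the difference in wording cannot be put down to shorthand.

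The pair 63.3% and 38.5% is the only basis for the 120. If the Background label is right, the calculation sets a control risk that counts deaths against an LTNIV risk that does not. That enlarges the assumed effect. The Discussion notes that the largest previous RCT found no effect, so a null result here is a real possibility. Readers would judge it against a claimed 80% power.

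**Working it through.** **Inputs.** Control 63.3% and LTNIV 38.5% (Sample size/power calculation); 60.2% and 38.5% for the earlier RCT (Background); alpha 0.05, power 0.80, dropout 20% (Sample size/power calculation); 1:1 allocation (Randomization); Cox and log-rank analysis by intention to treat (Data processing). Two-sided alpha is assumed, as the article does not state the sides.

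**1. Reproducing the plan's figure.**

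- Two proportions, unpooled: n per arm = (1.960 + 0.842)² × [p1(1−p1) + p2(1−p2)] / (p1−p2)² = 7.849 × (0.2323 + 0.2368) / 0.0615 = 59.9. That is 60 per arm, 120 in total, as stated.
- Log-rank (Schoenfeld, constant hazards): HR = ln(0.615)/ln(0.367) = 0.485. Events = 4 × 7.849/(ln 0.485)² = 60. Mean event risk = (0.633 + 0.385)/2 = 0.509. N = 60/0.509 = 118.
- Dropout: 120/0.8 = 150, as stated.

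The arithmetic is sound. With 63.3% in the control arm, 80% power at 120 evaluable needs an HR of about 0.49.

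**2. If 38.5% is a one-year risk of repeat AHRF only.** The composite risk in the LTNIV arm cannot be below 38.5%. It equals 38.5% only if no LTNIV patient dies within the year without a prior repeat AHRF. The article does not give the frequency of such deaths. I therefore assume a risk m, independent of AHRF:

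LTNIV composite = 1 − 0.615 × (1 − m)

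Power is given as a range from the pooled two-proportion test (lower) to the log-rank formula (upper). The log-rank formula is Φ(√(d/4) × |ln HR| − 1.960), with d = N × mean event risk. For m = 5% and N = 120: HR = ln(0.584)/ln(0.367) = 0.536, d = 120 × 0.524 = 62.9, and power = Φ(3.97 × 0.623 − 1.960) = 70%. Control risk is 63.3% throughout.

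| Assumed LTNIV deaths without AHRF | LTNIV composite | HR | Power, 120 evaluable | Power, all 150 contributing fully |
|---|---|---|---|---|
| 0% (implied by the plan) | 38.5% | 0.485 | 78-81% | 87-89% |
| 5% | 41.6% | 0.536 | 67-70% | 76-79% |
| 10% | 44.7% | 0.590 | 54-56% | 63-66% |
| 15% | 47.7% | 0.647 | 40-43% | 48-51% |

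The last column is an upper bound. Under intention to treat, dropouts count until they are censored, so the truth lies between the two power columns.

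For scale only: the Background cites 49.1% one-year mortality after AHRF, and reports that 20% of the authors' own 20 LTNIV patients died within a year. Some of those deaths may have followed a repeat AHRF, so neither figure is a value for m.

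**3. If 38.5% is the composite.** The Background is then misworded and 63.3% v 38.5% gives the stated 80%, as a contrast across two studies. If the 60.2% is the composite too, that RCT's own contrast is a natural sensitivity figure. HR = ln(0.615)/ln(0.398) = 0.528. The requirement is 7.849 × (0.2396 + 0.2368)/0.0471 = 79.4 per arm, 159 in total, or 77 events/0.4935 = 156 by log-rank. Power is 67-69% at 120 evaluable and 76-79% at 150.

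**The case against.** The strongest reply is that the article does not show which label is right. If the sample-size section is right, only the Background needs correcting. Taking the control risk from a study of AHRF survivors instead of the RCT's own control arm is a planning choice, not an error; the two control figures differ by 63.3 − 60.2 = 3.1 points. This stands. A reader might infer that the assumed effect is too large under either label, or that the trial does not have 80% power. The documents support neither inference.

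A second reply is that the Background gives 38.5% per year and calls it a rate. Read as a constant hazard (an assumption), it is a one-year AHRF risk of 1 − exp(−0.385) = 32.0%. A composite of 38.5% would then leave room for 1 − 0.615/0.680 = 9.6% independent deaths without AHRF. So the floor argument needs the figure to be a cumulative risk. This also stands, but it does not rescue the 80%: the sample-size section uses 38.5% as a one-year composite risk, and on this reading nothing in the article shows that it is one.

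Third, a reader might take 67-69%, from 60.2% v 38.5%, as the corrected power. On the Background's wording both of those are repeat-AHRF figures, so that would be power for AHRF alone and not for the primary composite. It is usable only if 38.5% and 60.2% prove to be composite risks.

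Finally, power at 120 is the cautious end, because all 150 contribute follow-up to a log-rank analysis. At 5% added deaths the upper bound almost reaches 80%; at 10% and 15% it does not.

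**Conclusion.** The point holds as an inconsistent planning input, not as a miscalculation. The 120 and the 150 follow correctly from 63.3% v 38.5%, but the article itself contradicts what the 38.5% measures. The 80% power for death or repeat AHRF is therefore unsupported as written; it is not proven false.

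The size depends on the answer. If 38.5% is a one-year risk of repeat AHRF only, power at 120 evaluable falls to about 67-70%, 54-56% or 40-43% for 5%, 10% or 15% deaths without AHRF in the LTNIV arm. Those death rates, and their independence from AHRF, are assumptions. If 38.5% is the composite, the 80% stands, resting on a comparison across two studies. The primary outcome and its analysis are unaffected. This should be corrected, but it does not call the design into question.

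**What to change.** 1. Check the cited RCT and reconcile the Background with the sample-size section. State whether 38.5% is repeat AHRF only or death or repeat AHRF, and whether it is a rate or a one-year cumulative risk.
2. If it is repeat AHRF only, restate power at the planned size with a composite risk in both arms. Give a short table over a declared range of LTNIV composite risks, with the assumed death rates shown, at 120 evaluable and at 150 as the upper bound.
3. If it is the composite, correct the Background and say that the 80% rests on a cross-study contrast. Add 60.2% v 38.5% as a sensitivity figure, provided that the 60.2% is also the composite.
4. In either case, state that 80% power at 120 evaluable needs an HR of about 0.49 with a 63.3% control risk.

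The cost is a few sentences, a recalculation and probably a less favourable power statement. Enrolment, conduct and analysis need not change.
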